**Methods/Design:**

A prospective cohort of 300 COPD patients in all GOLD stages will be constructed. Patients will receive usual multidisciplinary COPD care including guideline-directed physical therapy. Patients in this cohort who have GOLD stage 2 to 4 (post-bronchodilator FEV_1_/FVC < 0.7 and FEV_1_ < 80% of predicted), who receive reimbursement by health insurance companies for physical therapy (post-bronchodilator Tiffeneau-index < 0.6) and who experience a COPD exacerbation will be asked within 56 days to participate in a cohort-nested prospective randomised controlled trial (RCT). In this RCT, the intervention group will receive a strict physical therapy programme for patients with COPD. This protocol-directed physical therapy (pdPT) will be compared to a control group that will receive sham-treatment, meaning no or very low-intensity exercise training (ST). An economic evaluation will be embedded in the RCT. Anthropometric measurements, comorbidities, smoking, functional exercise capacity, peripheral muscle strength, physical activity level, health related quality of life, patients’ perceived benefit, physical therapy compliance, motivation level, level of effective mucus clearance, exacerbation symptoms and health care contacts due to COPD will be recorded. Follow-up measurements are scheduled at 3 and 6 weeks, 3, 6, 12 and 24 months after inclusion.

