### Study population

The study population consists of patients who are treated by COPD-specialised physical therapists, after referral by a general practitioner (GP) or pulmonologist. Physical therapy practices, GPs and pulmonologists, in southern districts of the Netherlands, who are willing to participate in the study, will be recruited. Once a patient is referred to a participating physical therapy practice (with post-bronchodilator FEV_1_/FVC < 0.7, GOLD 1–4), the patient will be asked to participate in the COPD cohort study. Patients in the cohort are monitored for health outcomes and exacerbation occurrence. Participants for the RCT will be recruited within the cohort by physical therapists, as soon a patient suffers from an exacerbation. Additionally, advertisements in local papers in southern regions of the Netherlands are used to reach potential COPD patients for the RCT who were missed out on inclusion with the former recruitment method. Those patients who are reached through advertising and presenting with an exacerbation will be recruited for the RCT by the researcher, while the mechanisms for alert and continuous trial recruitment are automatically organized within the cohort. By means of this unique cohort-nested RCT design (Figure 1), the likelihood that patients with a COPD exacerbation will be picked up is higher. A flowchart of the RCT is presented in Figure 2.

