The level of dyspnoea (MRC), effective mucus clearance, physical activity in daily life and motivation will be assessed by standardised questions from the KNGF guidelines [35]. Furthermore, to estimate the patients’ perceived benefit of the physical therapy, the Global Perceived Effect (GPE) will be scored by patients on a 9-point scale [35]. Objective assessment of physical activity in daily life will be done by means of an accelerometer-based activity monitor (Dynaport MoveMonitor) [50].

Height, weight, Body Mass Index (BMI) and Fat Free Mass (FFM) will be measured. The peripheral muscle strength of the patient will be measured as maximal voluntary isometric contraction (MVIC) of the dominant hand, shoulder abduction and knee extension (m. quadriceps), tested in standardised positions by means of the break method by a handheld dynamometer [42,51]. Functional exercise capacity is measured by the six-minute walk test (6MWT), in accordance with the guidelines by the American Thoracic Society [52]. If a straight floor-walking course of 30 metres is not available in the physical therapy practice, a course with a distance of 10 metres is the required minimum [35]. Outcome is measured by total walking distance in metres (6MWD) and in percentage of the predicted value. Reference equations by Hill et al. (2011) will be applied to calculate the predicted value if a straight 30 metre walking course was used, whereas reference equations for a straight 10 metre walking course may be necessary to develop within this study, as no reference equations exist for this frequently used test layout [53]. During the walk test, perceived fatigue and dyspnoea will be measured on a modified Borg scale ranging from zero (nothing at all) to ten (very, very severe) [42]. Transcutaneous oxygen saturation and pulse rate will be measured with a finger pulse oximeter (Onyx 9500) [52]. The modified Get Up and Go test (mGUG) is used to measure basic functional mobility. The outcome is the time it takes a subject to stand up from a chair and walk a distance of 10 metres [54]. After the mGUG, perceived exertion is measured with the modified Borg scale.

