### Data analysis

#### *Clinical effectiveness*

The descriptive characteristics are presented quantitatively as mean (±standard deviation) or median (5^th^ - 95^th^ percentile), depending on the data distribution, whenever the variable is continuous or as a percentage whenever the variable is dichotomous or categorical. Data will be analysed with SPSS-19. Assumptions accompanying the following statistical methods will be checked and all data analyses will be applied by a blinded analyst.

Data from the RCT will be analysed to examine intervention main effect on the counts for the primary outcome (exacerbation frequency) and the secondary outcomes. All exacerbations from each patient will be used as the dependent outcome to evaluate the effect of physical therapy at the end of the intervention (12 months) and follow-up (24 months). Measurement moments for secondary outcomes are baseline, three and six weeks, three, six, twelve and twenty-four weeks. The effects of the variable of primary interest, physical therapy (pdPT), will be analysed in a generalized linear model (GLM) for group (intervention vs. control) analysis of covariance with adapted regression for count data distribution. Analyses of secondary outcomes will be done with linear regression analysis and generalized linear models. Since exacerbation outcome in the RCT is measured with two methods, analyses will be based on the event-based approach, on the symptom-based approach and on a combination of both. Potential confounding by variables like, age, gender, GOLD stage, smoking, physical activity in daily life, exacerbation history, severity of latest exacerbation, and comorbidity, will be controlled for. Results from a ‘per-protocol’ and an ‘intention-to-treat’ principle will be compared. At a minimal statistical power of 80%, p-values smaller than 0.05 will be considered as significant.

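### 6MWD in % predicted has a reference equation only for the 30 m course; for the 10 m course the protocol points to equations from a study in which every described participant has COPD

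*Protocol article*

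**What the plan says.** All of the following is from the protocol article.

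- **Outcome scales** (Secondary outcome measures): "Outcome is measured by total walking distance in metres (6MWD) and in percentage of the predicted value".
- **Course length** (same section): 30 m is the standard. Where a practice has no such course, "a course with a distance of 10 metres is the required minimum". Intermediate lengths are therefore allowed.
- **30 m equation** (same section): a published set of reference equations "will be applied to calculate the predicted value if a straight 30 metre walking course was used".
- **10 m equation** (same section): "reference equations for a straight 10 metre walking course may be necessary to develop within this study, as no reference equations exist". The same sentence describes the 10 m layout as one in frequent use.
- **Participants**: the abstract says "A prospective cohort of 300 COPD patients in all GOLD stages will be constructed", and Study population says "The study population consists of patients who are treated by COPD-specialised physical therapists". RCT patients must be in GOLD stage 2 to 4 with a recent exacerbation. No healthy or other non-COPD sample is described.
- **Analysis** (Clinical effectiveness): secondary outcomes are analysed by linear regression and generalized linear models. The adjustment list opens with "Potential confounding by variables like, age, gender, GOLD stage, smoking, physical activity in daily life". Course length is not among the examples given.
- **Randomisation** (Randomisation and blinding): 1:1, stratified by exacerbation severity and GOLD stage.

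**The concern.** A percentage of predicted is useful because the denominator is an external norm. The protocol uses the term in that sense elsewhere: FEV1 below 80% of predicted is an inclusion criterion, and the record system alerts the therapist when peripheral muscle strength falls below 80% of predicted. For 6MWD, the protocol has such a denominator for one course length only. For the other layout it names, the only route offered runs through the study itself, and the study as described holds only patients with the disease.

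An equation fitted to those patients predicts what a COPD patient of that age, sex and build walks. The resulting percentage ranks a patient among COPD patients and does not show the shortfall from normal. Placed beside the 30 m values, it is a different quantity under the same name, and which one a patient receives would depend on the length of the practice's corridor. At stake is the meaning of one expression of a secondary outcome across sites.

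**Working it through.** There is no plan figure to reproduce here. The check is a reading of the text plus two illustrations with assumed values.

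**1. Which tests have a defined % predicted?**

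| Course used | Allowed | Equation |
|---|---|---|
| 30 m | yes | published, named |
| between 10 m and 30 m | yes, since 10 m is a minimum | none mentioned |
| 10 m | yes | none exists; may be developed within the study |

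The cohort (GOLD 1 to 4) and the RCT (GOLD 2 to 4) contain only COPD patients. The share of practices without a 30 m course is not given.

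**2. What would an equation fitted to these patients return?**

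Least squares with an intercept makes the mean predicted distance equal the mean observed distance in the fitting sample. Mean % predicted is then close to 100% in that sample (only close, because a mean of ratios is not a ratio of means).

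For contrast, assume a patient who walks 400 m and a healthy reference that predicts 550 to 600 m:

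- 400/550 = 73% and 400/600 = 67%
- gap to 100%: about 27 to 33 points
- the same gain in metres is divided by 400 instead of 550 to 600, so it counts 550/400 = 1.38 to 600/400 = 1.5 times as many points

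The distances are illustrative, and the documents do not describe the sample behind the 30 m equation. That it is a healthy one is an assumption.

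**3. What does mixed course length do to the comparison in metres if it is left out of the model?**

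Assumed, because the documents give none of these: between-patient SD 80 to 120 m; course effect d = 20 to 60 m; share p on the short course 20% to 50%. From the protocol: 79 patients per arm before the drop-out allowance.

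*Variance.* Total variance = SD² + p(1 − p)d².

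- Smallest: 0.2 × 0.8 × 20² = 64; 64/120² = 0.4%
- Largest: 0.5 × 0.5 × 60² = 900; 900/80² = 14%

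*Power.* Power = Φ(δ / (σ√(2/79)) − 1.96), with δ assumed to be 0.45 SD.

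- No course effect: 0.45/√(2/79) = 2.83; Φ(0.87) = 81%
- Largest inflation: σ = √(6400 + 900) = 85.4 and δ = 36; 36/(85.4 × 0.159) = 2.65; Φ(0.69) = 75%
- Smallest inflation: still about 81%

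*Chance imbalance.* The SE of the between-arm difference in the share on the short course is √(2p(1 − p)/79).

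- p = 0.2: SE 0.064; 1.96 × 0.064 × 20 m = 2.5 m
- p = 0.5: SE 0.080; 1.96 × 0.080 × 60 m = 9.4 m

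So the 95% limit for the shift lies between about 2.5 and 9 m. The expected shift under randomisation is zero.

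**The case against.** The protocol is candid about the gap. Its wording is conditional: equations may be needed. It does not say that they would be fitted to the trial patients, and it does not rule out a separate reference sample. This stands, and it is why the point cannot be put as % predicted being impossible to derive at 10 m sites. What remains is that the only source indicated is the study, and the study as described has no non-COPD participants.

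A reader might also infer that 10 m and 30 m distances are pooled without adjustment. The documents do not say so. The covariate list is open-ended, so leaving course length out of the examples does not exclude it, and detail of this kind may sit in an analysis plan that is not shown.

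Nor do the documents support reading mixed course lengths as a source of spurious treatment effects. Course length follows from what the practice has available, allocation is randomised 1:1, and chance imbalance is part of ordinary sampling error. Follow-up tests take place at the physical therapy practice (Planning of outcome assessment), and nothing suggests that patients switch courses. Not stratifying by practice is a design choice, and the protocol gives a reason for the strata it uses.

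Finally, 6MWD is one secondary measure among many, and metres are already collected for everyone. That limits the weight of the point but does not give the % predicted scale a definition at practices without a 30 m course.

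**Conclusion.** The point holds in a limited form. A declared outcome scale, 6MWD in % predicted, has a usable denominator only for 30 m tests. For the 10 m course the protocol refers to equations that may come from the study and names no source sample other than COPD patients. For intermediate lengths it names nothing. If equations were fitted to the study's own patients, 10 m and 30 m percentages would not be comparable.

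The 27 to 33 point gap shows the kind of difference to expect. It is not an estimate for this trial: it depends on assumed distances, on a healthy reference behind the 30 m equation, and on an equation fitted to patients.

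In metres, leaving course length out of the model would be a matter of precision: 0.4% to 14% more variance, and power of about 81% falling to 75% at worst under the assumed ranges, with no expected bias. Exacerbation frequency, the primary outcome, is not touched.

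**What to change.** - Do not derive % predicted for courses shorter than 30 m from the study's own COPD patients. Report % predicted only for 30 m tests, unless 10 m equations from a non-COPD reference sample are available; in that case, name the sample.
- State that 6MWD in metres is the exercise-capacity outcome for the between-arm comparison in all patients.
- Record the course length at each test, and require the same length at every visit for a given patient.
- Include course length and baseline 6MWD as covariates in the 6MWD model.

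The cost is a few lines of protocol and analysis text and one recorded field. The downside is that % predicted is not available at practices without a 30 m course.

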#### *Planning of outcome assessment*

In all eligible patients, entering the cohort and the RCT, baseline assessment will be performed. In the baseline assessment, demographic variables, anthropometric data, healthcare/medical variables, lifestyle factors, health related quality of life and clinical status will be recorded of the participants.

The lung function of the patients is already assessed by the GP/pulmonologist or assistant, by means of pulmonary function tests, as part of standard procedure in patients with COPD. Forced expiratory volume in one second (FEV_1_ (L)), forced vital capacity (FVC (L), the FEV_1_/FVC ratio and Tiffeneau-index (FEV_1_/VC) are measured by means of post-bronchodilator spirometry and are known to the physical therapist in order to construct a tailored-made programme adjusted to the severity of the pulmonary component of the disease. The clinical status, maximal exercise capacity and physiological restrictions of the patients should in most cases have been assessed by a maximal CPET and communicated to the physical therapist in order to enable the physical therapist to construct a safe and tailored-made programme for the patient. If the clinical status of the patient in the RCT is not yet assessed in the hospital or rehabilitation clinic, the treating physical therapist will be asked to refer the patient for a maximal CPET to a sports medicine physician, who is contacted by the researcher.

After the baseline visit, participants in the cohort will be assessed every three months for 12 months or longer. Participants from both the experimental and the control group in the RCT will be measured at three and six weeks, and three, six, twelve and twenty-four months during follow-up visits at the physical therapy practice for various outcome measures (Figure 3).

**Figure 3 F3:**
[figure not shown]
**Planning of outcome measurements in the RCT.** The diary cards are not included in the Figure, but they are used by the patient every day of every month until T_6_. In the cohort, the baseline measurement is followed by the same measurements as on T_3_ in the RCT and are repeated every three months for at least twelve consecutive months. Definition of abbreviations: T_0_ = baseline measurement; T_1_ – T_10_ = consecutive measurements in time after the baseline measurement; A = Anthropometric measures; B = Bicycle test results (maximal cardiopulmonary exercise test (CPET)); S = Spirometry results; 6 = 6MWT + Borg score and mGUG + Borg; M = peripheral muscle strength; P = physical activity in daily life with accelerometer; Q = CCQ*, CRQ-SR, EQ-5D*, DS14, MRC and level of effective mucus clearance, level of motivation, physical activity, physical therapy compliance*; C = questionnaire to assess direct and indirect costs; and G = Global Perceived Effect*. Measurement occasions are explained in the Table above the Figure. *The only measurements on T_1_ and T_2_.

In the RCT, prospective daily diary cards are distributed every month for twenty-four consecutive months and are returned by the patient at the end of every month. The retrospective questionnaire on the use of health care is send to the patient once every three months for twenty-four consecutive months.

### Data analysis

#### *Clinical effectiveness*

The descriptive characteristics are presented quantitatively as mean (±standard deviation) or median (5^th^ - 95^th^ percentile), depending on the data distribution, whenever the variable is continuous or as a percentage whenever the variable is dichotomous or categorical. Data will be analysed with SPSS-19. Assumptions accompanying the following statistical methods will be checked and all data analyses will be applied by a blinded analyst.

Data from the RCT will be analysed to examine intervention main effect on the counts for the primary outcome (exacerbation frequency) and the secondary outcomes. All exacerbations from each patient will be used as the dependent outcome to evaluate the effect of physical therapy at the end of the intervention (12 months) and follow-up (24 months). Measurement moments for secondary outcomes are baseline, three and six weeks, three, six, twelve and twenty-four weeks. The effects of the variable of primary interest, physical therapy (pdPT), will be analysed in a generalized linear model (GLM) for group (intervention vs. control) analysis of covariance with adapted regression for count data distribution. Analyses of secondary outcomes will be done with linear regression analysis and generalized linear models. Since exacerbation outcome in the RCT is measured with two methods, analyses will be based on the event-based approach, on the symptom-based approach and on a combination of both. Potential confounding by variables like, age, gender, GOLD stage, smoking, physical activity in daily life, exacerbation history, severity of latest exacerbation, and comorbidity, will be controlled for. Results from a ‘per-protocol’ and an ‘intention-to-treat’ principle will be compared. At a minimal statistical power of 80%, p-values smaller than 0.05 will be considered as significant.

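### Secondary-outcome times are printed in weeks instead of months, and the named models carry no stated provision for repeated visits or for the outcome's own baseline value

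*Protocol article*

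**What the plan says.** All references are to the protocol article.

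- **Method.** Under *Clinical effectiveness*: "Analyses of secondary outcomes will be done with linear regression analysis and generalized linear models".
- **Times in the analysis section.** The same paragraph says: "Measurement moments for secondary outcomes are baseline, three and six weeks, three, six, twelve and twenty-four weeks".
- **Times elsewhere.** *Planning of outcome assessment* says that both RCT groups "will be measured at three and six weeks, and three, six, twelve and twenty-four months". The abstract's *Methods/Design* agrees: "Follow-up measurements are scheduled at 3 and 6 weeks, 3, 6, 12 and 24 months after inclusion". The *Economic evaluation* section uses CCQ and CRQ-SR at 12 months and computes EQ-5D utilities at 12 and 24 months.
- **Outcomes by visit.** The legend of Figure 3 stars CCQ, EQ-5D, therapy compliance and Global Perceived Effect, and explains the star as "The only measurements on T_1_ and T_2", that is, the visits at 3 and 6 weeks.
- **Covariates.** "Potential confounding by variables like, age, gender, GOLD stage, smoking, physical activity in daily life, exacerbation history, severity of latest exacerbation, and comorbidity" are to be controlled for. The word *like* leaves the list open. Analysis of covariance is mentioned for the physical therapy effect, as "analysis of covariance with adapted regression for count data distribution", without saying which covariates enter.
- **Repeated measures.** RM ANOVA is expanded in the abbreviation list, but the analysis text does not use it.

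**The concern.** Three things in one paragraph do not fit the data that will be collected.

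First, the visit list is wrong as printed. Read literally, the last secondary measurement falls at 24 weeks, well before the one-year treatment ends.

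Second, each patient contributes several correlated values per outcome. Linear regression and generalized linear models in their ordinary form treat observations as independent. The paragraph does not say whether visits are analysed together or one at a time, or which visit carries the main comparison.

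Third, the outcome's value at baseline is collected and is usually the strongest predictor of its later value, yet it is not among the eight covariates named.

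Health status and quality of life are part of the stated study aim, so these analyses matter. Depending on how the gaps are filled, the cost is either standard errors that are too small or precision given away.

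**Working it through.** **1. Visit times side by side**

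| Source | Early visits | Later visits |
|---|---|---|
| Abstract | 3, 6 weeks | 3, 6, 12, 24 months |
| Planning of outcome assessment | 3, 6 weeks | 3, 6, 12, 24 months |
| Clinical effectiveness | 3, 6 weeks | 3, 6, 12, 24 weeks |

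Four of the six follow-up times carry the wrong unit, and 3 and 6 weeks then appear twice. Twenty-four weeks is 24 × 7 / 30.44 = 5.5 months.

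**2. Follow-ups per outcome**

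There are six scheduled visits after baseline. Only the starred items are measured at the first two. CCQ and EQ-5D therefore have six follow-ups. CRQ-SR, 6MWD, muscle strength and activity have at most 6 − 2 = 4.

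**3. If all follow-ups were stacked as independent**

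The article gives no figure for the secondary analyses to reproduce, and no within-patient correlation. I assume an equal correlation ρ between any two visits, with a range. For m visits and a group main effect:

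- design effect = 1 + (m − 1)ρ
- true two-sided type I error = 2[1 − Φ(1.96 / √design effect)]

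| m | ρ | Design effect | True error at nominal 5% |
|---|---|---|---|
| 6 | 0.4 | 3.0 | 26% |
| 6 | 0.6 | 1 + 5 × 0.6 = 4.0 | 2[1 − Φ(0.98)] = 33% |
| 6 | 0.7 | 4.5 | 36% |
| 4 | 0.4 | 2.2 | 19% |
| 4 | 0.6 | 1 + 3 × 0.6 = 2.8 | 2[1 − Φ(1.17)] = 24% |
| 4 | 0.7 | 3.1 | 27% |

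A simulation with 79 patients per arm and 4,000 runs per setting gave 0.154, 0.216, 0.267 and 0.284 for four follow-ups, and 0.206, 0.302, 0.337 and 0.384 for six, at ρ = 0.3, 0.5, 0.7 and 0.8. The formula gives 0.155, 0.215, 0.266 and 0.288, and 0.215, 0.295, 0.356 and 0.381. All agree within 0.02.

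**4. If each visit is analysed separately**

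No within-patient term is needed, and the error per test stays at 5%. A patient without a value at that visit contributes nothing to that test. The only drop-out figure is the 20% in the primary sample size. Applied here as an assumption, it leaves 100 × 0.80 = 80 per group.

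**5. Adjusting for the outcome's own baseline value**

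For a continuous outcome with baseline correlation r (assumed), the residual variance is multiplied by 1 − r², which is worth 1/(1 − r²) times as many patients without adjustment.

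| r | Variance factor | Variance cut | Equivalent extra patients |
|---|---|---|---|
| 0.4 | 0.84 | 16% | 1/0.84 − 1 = 19% |
| 0.6 | 0.64 | 36% | 1/0.64 − 1 = 56% |
| 0.7 | 0.51 | 49% | 1/0.51 − 1 = 96% |

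**The case against.** The strongest reply is that this is a condensed article with one clear slip in it. The abstract and the assessment plan agree on months, no one would design a schedule with 3 and 6 weeks listed twice, and the economic section still uses 12 and 24 months. That largely stands. A reader might infer that the end of treatment and the two-year follow-up have been dropped as analysis times; the documents do not support this. The contradiction still needs correcting, because it sits in the only sentence that gives measurement times for the clinical secondary analyses.

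A reader might also infer that the plan ignores within-patient correlation and so runs a type I error near one third. The text does not say this. It never states that visits will be pooled, it promises to check model assumptions, and regression at a single visit is valid. The inflation is conditional on stacking.

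Nor is baseline adjustment excluded. The covariate list is open, baseline is listed as a measurement moment, and physical activity is both a named covariate and a secondary outcome. Omitting the baseline value from a randomised comparison costs precision and causes no bias in expectation.

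Finally, such detail often sits in an analysis plan that is not shown. That excuses silence on the covariance structure. It excuses less a text that names a class of models and attaches wrong times to it. The planned comparison of intention-to-treat and per-protocol results does not settle the missing-visit question, since neither principle says what happens to a patient with no value at a visit.

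**Conclusion.** The point holds in a limited form. The weeks/months contradiction is certain and rests on no assumption. The rest concerns what the paragraph leaves unsaid: the models named make no stated provision for repeated measurements, and the outcome's own baseline value is not named as a covariate.

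The type I error figures (33% for six follow-ups, 24% for four, at an assumed correlation of 0.6) apply only if visits are stacked as independent. The six-visit figure does not apply to CRQ-SR, 6MWD, strength or activity. Under visit-wise analysis the cost is lost patients and lower precision.

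The gain from baseline adjustment, equal to about 19 to 96% more patients, rests on assumed correlations of 0.4 to 0.7 and on continuous outcomes with a baseline value. It is an efficiency gain; an analysis without it would still be valid. This is worth changing because the improvement is nearly free.

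**What to change.** 1. Correct the list in *Clinical effectiveness* to baseline, 3 and 6 weeks, and 3, 6, 12 and 24 months.
2. Adjust each continuous secondary outcome for its own baseline value and for the stratification factors, exacerbation severity and GOLD stage. GOLD stage and severity of the latest exacerbation are already among the named covariates.
3. State how repeated visits are handled. A model that allows for within-patient correlation, for example a mixed model for repeated measures, keeps patients who miss one visit but attend others. Visit-wise ANCOVA is an acceptable alternative if chosen in advance.
4. Name 12 months, the end of treatment, as the main contrast for these outcomes, with the other visits as supporting results.

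The cost is a few sentences and slightly more programming. No new data, visits or patients are needed.
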